### Randomization and blinding

Block randomization will be implemented for this study, with varying block sizes of 2 to 4, to prevent selection bias and predictability. The randomisation list will be computer-generated and concealed by a researcher (author identifying information) who will have no direct contact with the participants. A research assistant will enroll participants and assign them to either the “Taekwondo training with elements of music therapy” (n = 36) or the “Taekwondo training alone” (n = 36) group in a 1:1 ratio. Given the behavioral nature of the intervention, blinding will not be feasible for the participants and parents. They will be unaware of their group allocation in the recruitment process until they provide written consent. The coaches, the trial coordinators, and the research personnel who review and code the video recording of the training sessions will also not be blinded to the group allocation. There will be concealment of the allocation sequence so that the trial coordinators will not know the group allocation of an individual before they consent them. To minimize measurement bias, all other research personnel involved in data collection, processing, and analysis will be blinded to group allocation.

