#### 1. Immediate effects in the training sessions

*1*.*1 Engagement in the training sessions (primary outcome)*. Training sessions will be videotaped and coded. The direct observation component of the Revised Individual Child Engagement Record (ICER-R) system will be applied to record individual children’s engagement [35,36] during the training sessions. The ICER-R uses a 15-second momentary time sampling approach and involves the coding of types of engagement, the occurrence of interaction with partners (coach or peers), and whether the child was physically prompted. The types of engagement being coded at each 15-second interval are active engagement, passive engagement, active non-engagement, and passive non-engagement. Anecdotal information including emotional response was recorded during the observation for qualitative analysis. The mean inter-observer agreement is 83% for engagement, 88.7% for interaction occurrence, and 96.8% for interaction partner [35]. The engagement during the training session is expected to be the most sensitive to changes induced by music therapy, as the music is specifically designed to match the rhythm and dynamics of the Taekwondo movements. This is supported by two previous studies showing that incorporating musical elements into exercise training/activities significantly increased the engagement level in children with autism [18,26].

*1*.*2 Enjoyment state*. The Children’s Emotional Manifestation Scale (CEMS) will be used to assess the children’s emotional state at the end of each training session. Children will be asked to select which cartoon facial expression most represents their emotional state. The numbers obtained for each category are added together to obtain the total score. High scores indicate the manifestation of more negative emotional behavior. The interrater reliability coefficient of the CEMS is 0.96, and its internal consistency has an alpha coefficient of 0.92 [37].

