#### 2. Overall effects of the Taekwondo training program

The following assessments will be conducted by an assessor experienced in the measurement tests and blinded to group allocation at baseline, after completion of the 10-week program, and at 2-month follow-up at the university laboratory and the Taekwondo training center.

*2*.*1 Gross motor skills*. The assessment will include gross motor composites that measure manual coordination, body coordination, and strength and agility from the Bruininks–Oseretsky Test of Motor Proficiency-2 (BOT-2) [41]. Manual coordination will be evaluated through two tasks that test upper-limb coordination. Body coordination will be assessed through seven tasks that test bilateral coordination and nine tasks that test balance. Strength and agility will be evaluated through five tasks that assess running speed and agility and five tasks that evaluate strength. A trained assessor will demonstrate each item to the children during the assessment. Visual aids will be displayed on an easel for the children’s reference. The raw scores of each task will be converted to the point scores. The point scores for each task within the same gross motor composite will be added up as a sub-score. This allows for comparisons to be made across different assessment times. The BOT-2 had good test-retest reliability and internal consistency of the total scale, with an ICC of 0.99 (95% confidence interval) and Cronbach’s alpha coefficient of 0.92 [42].

*2*.*2 Taekwondo skills performance*. A scoring system was modified for use in this project with reference to the international Taekwondo referee scoring standard. This assessment will be carried out at the Taekwondo training center. Children’s performance for a set of selected Taekwondo moves and kicks will be observed and scored by two qualified referees. Both accuracy and overall presentation of the Taekwondo movement, stance, and techniques will be scored.

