*2*.*5 Social responsiveness scale*, *second edition (SRS-2)*. This scale will be completed by the parents. It is a 65-item autism rating scale widely used for identifying a spectrum of deficits in reciprocal social behavior, ranging from absent to severe, based on observations of a child’s behavior in various social settings. Scoring is on a four-point Likert scale with five subscales (social awareness, social cognition, social communication, social motivation, and autistic mannerism) [46]. Higher T-scores correspond to poorer social functioning. The questionnaire has an internal consistency of 0.95 and an inter-rater reliability of 0.77 [47].

*2*.*6 Strength and Difficulties Questionnaire (SDQ)*. The questionnaire will be completed by parents. There are 25 items in the SDQ, which consists of five scales, each with five items, for assessing children’s mental health status in terms of emotional, conduct, hyperactivity, peer problems, and prosocial behavior [48]. The questionnaire has an internal consistency coefficient of 0.81 and a test-retest reliability coefficient of 0.86 [48].

*2*.*7 Clinical global improvement (CGI) score*. The CGI-I will be completed by parents to evaluate children’s functional changes in daily life after completion of the 10-week program, and at 2-month follow-up [49]. The CGI-I consisted of 12 questions developed by our research team, which are focused on all core symptoms of ASD and covered the following aspects: (1) motor functioning; (2) children’s capability to follow instructions; (3) social, communication, and language understanding and expression; and (4) children’s capabilities for attention shifting, attention to complete a task, attention to details, and imagination. The CGI-I is rated on a 7-point Likert scale ranging from 1 (very much improved) to 7 (very much worse since the initiation of intervention), with 4 representing no change. A lower score for each item of the CGI-I indicates more favorable outcomes. In addition to these 12 questions, we modified the CGI-I in this study to include a question asking parents about the overall rating of their child and an open-ended question that enables parents to report their observations of their child after participation in this program.

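### The primary outcome is coded from video by staff who know the allocation, with no reason or safeguard given, so coder expectation could bias the main comparison

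*Protocol article*

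**What the plan says.** All references are to the protocol article.

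- **Source of the primary outcome** (section 1.1, Engagement): "Training sessions will be videotaped and coded". The coding system is the ICER-R, and "The types of engagement being coded at each 15-second interval are active engagement, passive engagement, active non-engagement, and passive non-engagement". The same observation also "involves the coding of types of engagement, the occurrence of interaction with partners (coach or peers), and whether the child was physically prompted".
- **Who codes it** (Randomization and blinding): "the research personnel who review and code the video recording of the training sessions will also not be blinded to the group allocation".
- **Reason offered** (same section): "Given the behavioral nature of the intervention, blinding will not be feasible for the participants and parents". The sentence does not mention the coders.
- **Everyone else** (same section): with the declared aim of limiting measurement bias, "all other research personnel involved in data collection, processing, and analysis will be blinded to group allocation".
- **Programme-level outcomes** (opening of section 2, Overall effects): "The following assessments will be conducted by an assessor experienced in the measurement tests and blinded to group allocation at baseline"; the sentence goes on to cover the post-programme and two-month visits.
- **Parent scales** (section 2.5, SRS-2): "This scale will be completed by the parents". Sections 2.6 (SDQ) and 2.7 (CGI-I) likewise name the parents as raters.

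**The concern.** The outcome that decides the trial has weaker protection than most of the secondary ones. Deciding whether a child is actively or passively engaged at a given instant is a judgement, and the people making it will know which arm they are watching. They will also know which answer the trial hopes for: section 1.1 expects engagement to respond most to the music, and the Discussion predicts more of it in the music arm.

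If that knowledge moves even a modest share of codes in one direction, the trial could report a benefit of music that comes partly from the coding. Unlike the blinding of children, parents and coaches, this exposure is not forced by the intervention, because the coding uses recordings. A plan that blinds its other data staff in order to limit measurement bias has accepted the principle but not applied it to its primary outcome.

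**Working it through.** **1. The provisions side by side**

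| Role | Blinded? | Reason given |
|---|---|---|
| Children and parents | No | Behavioural intervention |
| Coaches and trial coordinators | No | None specific to them |
| Video coders (primary outcome) | No | None |
| Assessor of programme-level tests | Yes | Limits measurement bias |
| Other data collection, processing and analysis staff | Yes | Limits measurement bias |

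The coders' knowledge of the arm is stated outright. It is not a detail that a condensed article has left to a fuller document.

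**2. Can the analysis remove a coding bias?** Let the true difference between arms be δ, and let coders who know the arm add b points to the music arm. The expected observed difference is then δ + b. The Statistical analysis section specifies a mixed model with intervention, time, their interaction and a random participant effect. A shift that is constant over sessions falls on the intervention term; one that grows or fades over sessions falls on the interaction. No term represents the coder's expectation, so δ and b cannot be told apart.

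**3. Can b be estimated from the document?** No.

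- The 83% agreement on engagement in section 1.1 comes from a cited source, not from this trial's coders.
- The remaining 17% (100 − 83) is disagreement between two observers. It has no direction and does not bound a directional bias.
- Agreement is over four states. A disagreement between active and passive non-engagement, for example, leaves the share of active engagement unchanged.
- The 11.8-point difference in the Sample size section (11.8 / 21.6 = 0.546, stated as 0.55) is time in vigorous exercise in a jogging study, which the article says correlates with engagement. It is not an engagement score.

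**4. Sensitivity only, with b assumed.** Borrow the SD of 21.6 from the Sample size section, set δ = 0, and compare two arm means by a normal two-sided test at 5%:

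se = 21.6 × √(2/n); P(reject) = Φ(b/se − 1.96) + Φ(−b/se − 1.96).

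With n = 36 per arm (72 recruited), se = 5.09. With n = 27 per arm (the stated minimum of 54), se = 5.88.

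| Assumed b (points) | False-positive rate, n = 36 | False-positive rate, n = 27 |
|---|---|---|
| 0 | 5.0% | 5.0% |
| 2 | 6.8% | 6.3% |
| 4 | 12.3% | 10.4% |
| 5 | 16.6% | 13.6% |
| 6 | 21.8% | 17.5% |
| 8 | 34.9% | 27.5% |

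A 45-minute session has 45 × 60 / 15 = 180 samples, so 5 points is 0.05 × 180 = 9 codes per session. The table shows what a shift would do if it occurred. It says nothing about whether it will or how large it would be, it borrows the SD of a different measure, and it is simpler than the planned model.

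**5. Is masking plausible?** The Intervention section gives the presence or absence of music as the only planned difference between arms, so removing the sound removes the main cue. The same section says that coaches in the music arm demonstrate in time with the music, and that children train in classes of six over 20 sessions. Some visible cues will therefore remain.

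**The case against.** The strongest reply is that masking may achieve little. Demonstrations in time with the music can be seen. If each class belongs to one arm, as music played to a whole class implies, a coder who identifies a class once may know its arm in every later clip, whatever the file label. Muting also removes speech that may help in judging engagement, and the ICER-R observation records interaction and prompting alongside it. All of this stands. It limits what the remedy can deliver, but it does not justify open coding: partial masking still leaves fewer codes exposed to expectation.

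Second, heart rate is recorded by device in every session and offers a comparison free of rater judgement. That is useful supporting evidence, but it measures something else and cannot correct a bias in the engagement codes.

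A reader might also infer three stronger claims, which the document does not support:

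- *That muting would be free.* Nothing in the article says so, or says that the ICER-R can be scored without sound. A second pass and different coders take time.
- *That the bias must fall wholly on the side of music and can be sized from the 83% agreement.* The direction is plausible given the stated hypothesis, but the article contains no evidence on coder behaviour, and the agreement figure cannot be turned into a bias.
- *That the plan passes parent reports off as blinded.* The lead-in to section 2 is loosely worded, but the article says elsewhere that parents are unblinded and that they complete SRS-2, SDQ and CGI-I. Read as a whole, it already discloses this.

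**Conclusion.** The point holds as a largely avoidable risk of detection bias on the primary outcome. It rests on three facts in the article: the outcome is a rater's judgement, the raters know the arm, and no reason or safeguard is given for them although other data staff are blinded. The bias plausibly favours the music arm, and the planned model cannot separate it from a true effect. Its size cannot be estimated from the document; the sensitivity table depends on assumed shifts and a borrowed SD and should not be cited as an estimate.

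The change is worth making before coding starts, because it is cheap and needs no additional children, visits or procedures. The wording about the assessor in section 2 is a minor note and adds no weight to the main point.

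**What to change.** 1. **Amend Randomization and blinding.** Engagement type is to be coded by existing research staff who do not attend the sessions and are not told the arm, from muted clips labelled by code number and presented in random order. Preferably these should not be the blinded assessor of the programme-level tests, whose own masking the clips could compromise.
2. **Add a later pass with sound** for interaction with partners and any other item that needs audio, once the engagement codes have been locked.
3. **Report inter-observer agreement by arm** on any double-coded clips.
4. **Acknowledge in the text that masking is partial.** Comparing muted with unmuted coding on a small subset would show what is lost without sound.
5. **Wording.** Limit the blinded-assessor sentence at the start of section 2 to the assessor-administered tests, and describe SRS-2, SDQ and CGI-I as unblinded parent reports.

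The cost is some file handling and extra coding time, verbal cues lost in the first pass, and masking that movement in time with the music or recognition of a class may break. The sample size, visits and training programme do not change.

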### Intervention

In both conditions, the participating children will attend 20 sessions of Taekwondo training. Except for the experimental manipulation (the presence or absence of music), children will receive the same level, skills, and duration of Taekwondo training across both conditions. The training will be administered in a group setting (six children per class), twice a week over 10 consecutive weeks. Each training session will last for 45 minutes and consist of warming-up exercises, hand movements, stance, foot movement techniques, a combination of stance and hand and foot techniques, and cool-down exercises. The teaching syllabus will follow the white belt (most junior) rank of the Taekwondo grading system. A qualified Taekwondo coach will conduct the training alongside a teaching assistant and two student assistants in each session.

In the Taekwondo training with elements of music therapy group, elements of music therapy will be incorporated into exercise training. Each piece of music will be tailor-made according to the rhythm, dynamic, tempo, duration, and associated feeling of a series of Taekwondo movements. For example, when forceful kicking is necessary, music with a rapid rhythm and strong, heavily accented beat will be applied. The music will serve to guide the motor patterns in a feedforward manner. The coaches will provide demonstrations that follow the tempo and rhythm of the specially composed music to guide the children in completing the Taekwondo movements. Short songs will also be composed, recorded, and played to accompany recurrent activities such as deep breathing and movement transitions. These short music pieces will offer cues to the children for recurrent activities and increase their success in effectively following the coach’s lead.

Teaching assistants will document attendance rate and any significant events during the study period. Participants who have been consistently absent will be contacted to investigate the reasons for their absence and to encourage regular attendance. If a participant drops out of the training sessions, they will still be invited to complete the post-training and 2-month follow-up assessments. All kinds of ASD-related concomitant trainings are permitted during the study period and information on these trainings will be recorded.

Given the behavioral nature of the intervention, we do not anticipate that participants will have any significant adverse event during the trial. We will monitor the rate of adverse events (e.g., injury during training session) for each of the treatment arms. To maximize the safety of the training sessions, we will use a standardized Taekwondo training protocol with a trainer-to-student ratio of 1 to 2 [34].

### Study measures

Demographic data will be collected, and the children’s behavioural and developmental characteristics associated with autism spectrum disorders will be evaluated at baseline using the Childhood Autism Spectrum Test (CAST) [34]. The effects of combining music with taekwondo training will be evaluated by measuring the immediate effects during the training sessions, and the overall effects of the training program on the outcome domains (Fig 3).

**Fig 3 pone.0315503.g003:**
[figure not shown]
Flow chart of the assessments across time.

#### 1. Immediate effects in the training sessions

*1*.*1 Engagement in the training sessions (primary outcome)*. Training sessions will be videotaped and coded. The direct observation component of the Revised Individual Child Engagement Record (ICER-R) system will be applied to record individual children’s engagement [35,36] during the training sessions. The ICER-R uses a 15-second momentary time sampling approach and involves the coding of types of engagement, the occurrence of interaction with partners (coach or peers), and whether the child was physically prompted. The types of engagement being coded at each 15-second interval are active engagement, passive engagement, active non-engagement, and passive non-engagement. Anecdotal information including emotional response was recorded during the observation for qualitative analysis. The mean inter-observer agreement is 83% for engagement, 88.7% for interaction occurrence, and 96.8% for interaction partner [35]. The engagement during the training session is expected to be the most sensitive to changes induced by music therapy, as the music is specifically designed to match the rhythm and dynamics of the Taekwondo movements. This is supported by two previous studies showing that incorporating musical elements into exercise training/activities significantly increased the engagement level in children with autism [18,26].

*1*.*2 Enjoyment state*. The Children’s Emotional Manifestation Scale (CEMS) will be used to assess the children’s emotional state at the end of each training session. Children will be asked to select which cartoon facial expression most represents their emotional state. The numbers obtained for each category are added together to obtain the total score. High scores indicate the manifestation of more negative emotional behavior. The interrater reliability coefficient of the CEMS is 0.96, and its internal consistency has an alpha coefficient of 0.92 [37].

*1*.*3 Physical activity level*. Participants will also wear an optical heart rate monitor (Polar OH1Electro Oy, Kempele, Finland) [38] on their forearms to measure their exercise heart rate as a reflection of their physical activity level during the training. Continuous heart rate data will be recorded for every session and expressed as the mean heart rate per minute. The measured exercise heart rate greater than 55% and less than 70% of each individual’s maximum heart rate (estimated as 220 minus age) will be used as individualized cutoffs for moderate- and vigorous-intensity cardiovascular workload, respectively [39].

*1*.*4 Rate of perceived exertion (RPE)*. Children will be asked to rate their exertion level at regular time points at each training session using the Borg 6-to-20 Scale, in which “6” indicates “no exertion at all” and “20” indicates “maximal exertion” [40]. High test-retest reliability (r = 0.89) was found for Chinese-translated versions of the Borg 6–20 Rating of Perceived Exertion (RPE) scale, and the perceived efforts in the RPE were shown to be significantly correlated with heart rate, power output, and oxygen consumption in children (p<0.01) [34].

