The insights provided by Srinivasan et al. (2014) and their conceptual framework implicate several causal links between music experiences and the development of language, communication, and social-emotional, behavioral, and motor skills in children with ASD [32]. In addition, Karageorghis’s (2016) theoretical model that addresses the antecedents, moderators, and consequences of music used in the exercise and sports domain [27,33] provided us with a framework for developing a model of combined music therapy and Taekwondo training to improve the physical and mental outcomes of children with ASD (S1 Fig). The predicted immediate effects observed during the exercise sessions include increased engagement and enjoyment, reduced perceived exertion, and increased physical activity level. The predicted overall benefits of Taekwondo training with elements of music therapy include improvements in gross motor skills, Taekwondo skills performance, attention, and social communication and behaviors.

Herein, we propose to test this hypothesis by conducting a randomized controlled trial to evaluate participating children in terms of the aforementioned study outcomes of a 10-week Taekwondo training program, with the presence or absence of music.

This trial has two objectives: (1) to examine the immediate effects of music therapy integrated into Taekwondo training sessions on the engagement and enjoyment during the training sessions in children with ASD; and (2) to examine the effects of a 10-week Taekwondo training program, with the presence or absence of music therapy, on the physical and mental outcomes in children with ASD. We hypothesize that the addition of musical elements specifically designed to match the rhythm and dynamic movement of the Taekwondo training will increase active engagement during the training sessions and provide extra benefits on physical and mental outcomes for children with ASD. The domains to be evaluated include the immediate effects during the exercise sessions of engagement (primary outcome), enjoyment, physical activity levels, and rates of perceived exertion, as well as the overall effects of the training program on gross motor skills, Taekwondo skill performance, executive function, and psychosocial functioning and behavioral problems.

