### Participants and study setting

Flyers containing information about the study will be sent to both autism support groups for parents in the community and randomly selected primary schools in Hong Kong. The parents of potential participants who are interested in the study will be invited to attend an introductory session about the project, after which they will be given an information sheet and parental written consent form. Children meeting the following eligibility criteria will be invited to participate in the study:

Inclusion Criteria:

Aged 7 to 9 years, andClinically diagnosed with ASD by a developmental pediatrician or clinical psychologist based on the Diagnostic and Statistical Manual of Mental Disorders (fifth edition)’s criteria for ASD [1].

Exclusion Criteria:

Any experience in Taekwondo training,Received music therapy within the previous 12 months,Learning difficulties and intellectual disabilities,Sensory disorders (blindness or deafness), orUnderlying congenital abnormalities or other diseases that limit their ability to engage in physical activities.

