### Statistical analysis

The participants’ characteristics and primary and secondary outcomes will be evaluated using summary statistics, including mean (SD), median (IQR), or proportions as appropriate, at multiple time points. The primary analysis will consist of an intention-to-treat analysis comparing the primary outcome (engagement) between the two intervention groups; specifically, a linear mixed-effect model will be used to investigate the effect of intervention (Taekwondo training with vs without elements of music therapy) over time (interaction between intervention and time) on the engagement in the training sessions, with a random effect for each participant. The effects of music therapy on the secondary outcomes measured during the training sessions, including physical activity levels, enjoyment state, and the rate of perceived exertion, will be tested by independent samples t-tests. Further, we will use a linear regression model to investigate the effect of intervention on these outcomes, adjusting for the following prognostic variables: age, sex, and BMI. A log transformation will be applied for any outcomes resulting in a skewed distribution.

For the other secondary outcomes measured before and after the training sessions, a linear mixed-effect model will be used to investigate the effect of intervention over time (interaction between intervention and time), with a random effect for each participantand adjusting for the following prognostic variables: age, sex, and BMI. The analyses will also evaluate the sustained benefits of the training by assessing the effect of the intervention on the secondary outcomes at the 2-month follow-up using the statistical methods described above. The significance level will be set at *p*< .05, and all analyses will be performed using SPSS (v25.0 for Windows; IBM, Armonk, NY, USA).

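### The vigorous-intensity heart-rate cutoff carries the wrong inequality: as written, vigorous means below 70% of maximum and overlaps with moderate

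*Protocol article*

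**What the plan says.** The rule is in the protocol article under "The measured exercise heart rate greater than 55% and less than 70% of each", item 1.3 (Physical activity level) of the section on immediate effects in the training sessions. Its parts are:

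- **Reference value:** each child's "maximum heart rate (estimated as 220 minus age").
- **Conditions, in order:** above 55%, then below 70%, of that maximum.
- **Classes, in order:** the two conditions "will be used as individualized cutoffs for moderate- and vigorous-intensity cardiovascular workload, respectively", with a citation to reference 39.
- **Form of the data:** the preceding sentence says "Continuous heart rate data will be recorded for every session and expressed as the mean heart rate per minute".

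The Statistical analysis section lists physical activity among the in-session secondary outcomes: "physical activity levels, enjoyment state, and the rate of perceived exertion, will be tested by independent samples t-tests". A covariate-adjusted linear regression follows. It does not say whether the analysed variable is the mean or an intensity class. The Introduction predicts the direction with music: "reduced perceived exertion, and increased physical activity level". No other section restates or corrects the cutoffs.

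**The concern.** The closing word of the sentence ties the first condition to moderate and the second to vigorous. Moderate therefore has a lower limit and no upper one, while vigorous has an upper limit and no lower one. The classes overlap in the middle of the range. Low heart rates during a session meet the vigorous condition, and the highest ones do not.

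The sentence is complete and says the cutoffs will be used, so this is a stated scoring rule and not a detail left to a fuller document. Physical activity is a named secondary outcome with a predicted direction. A vigorous class scored by this rule would shrink as children work harder. If the rule were corrected later without notice, the published protocol and the reported definition would disagree, and that could look like a changed outcome definition.

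**Working it through.** **Inputs.** Maximum heart rate is 220 − age and the cutoffs are 55% and 70% (both from item 1.3). Eligible ages are 7 to 9 years (Participants and study setting: "Aged 7 to 9 years"). The plan states no cutoff in bpm, so there is no figure of its own to reproduce.

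**Step 1: convert the cutoffs to bpm.** Cutoff = fraction × (220 − age).

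| Age | Maximum | 55% | 70% |
|---|---|---|---|
| 7 | 220 − 7 = 213 | 0.55 × 213 = 117.2 | 0.70 × 213 = 149.1 |
| 8 | 220 − 8 = 212 | 0.55 × 212 = 116.6 | 0.70 × 212 = 148.4 |
| 9 | 220 − 9 = 211 | 0.55 × 211 = 116.1 | 0.70 × 211 = 147.7 |

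**Step 2: apply the rule literally to an 8-year-old.** Moderate if the rate is above 116.6 bpm; vigorous if it is below 148.4 bpm.

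| Heart rate (bpm) | % of maximum | Moderate? | Vigorous as written? | Vigorous if the sign is reversed (above 70%)? |
|---|---|---|---|---|
| 90 | 42.5 | no | yes | no |
| 110 | 51.9 | no | yes | no |
| 120 | 56.6 | yes | yes | no |
| 147 | 69.3 | yes | yes | no |
| 150 | 70.8 | yes | no | yes |
| 170 | 80.2 | yes | no | yes |
| 190 | 89.6 | yes | no | yes |

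These rates classify identically at ages 7 and 9. No resting heart rate has to be assumed, because every rate below the 70% cutoff meets the literal vigorous condition.

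**Step 3: see which variables change direction.** Suppose heart rates in one arm shift upwards.

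- Share of readings below the 70% cutoff (vigorous as written): falls, against the prediction.
- Share of readings above the 55% cutoff (moderate as written): rises, with the prediction. In content this is a moderate-or-harder class.
- Mean heart rate: rises, with the prediction. The cutoffs do not enter it.

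Only the vigorous class is inverted.

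**Step 4: look for a reading that saves the sentence.** If 55% to 70% is one moderate band, vigorous is left undefined and the in-order matching has nothing to match. If both figures are lower limits, the words setting the 70% limit are wrong. Either way the text has to change.

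**The case against.** The strongest reply is that the slip may never reach a result. The only stated form of the data is a mean, and the Statistical analysis section names no intensity class and no time-in-zone measure. If the mean is what is tested, the cutoffs play no part. The intent is also fairly legible, since 55% goes with moderate and 70% with vigorous, and an analyst would probably notice the problem. All of this stands, and it limits the size of the point. It does not make the sentence right.

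Three stronger readings are tempting, and the documents do not support them:

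- **That the physical activity result as a whole will reverse.** Reversal needs an analysed or reported vigorous class, which the plan does not name. Even then the literal moderate class keeps its direction.
- **That the sample size is affected, because its planning effect comes from an earlier study of time in vigorous exercise.** That effect size is taken from the earlier study as a figure for engagement. The calculation does not use this trial's heart-rate cutoffs.
- **That a resting child will in practice be recorded as vigorous, and every rate outside 117 to 148 bpm misclassified.** The sentence concerns exercise heart rate in training and the plan gives no resting rate, although low in-session values would meet the literal rule. Misclassification can be counted only against intended bands, and the cited source for those is not at hand.

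**Conclusion.** The point holds as a wording error in the definition of one secondary outcome: the vigorous cutoff is stated with the wrong inequality. Across ages 7 to 9, every heart rate below about 148 to 149 bpm meets the vigorous definition as written. Rates between about 116–117 and 148–149 bpm meet both definitions, and higher rates count only as moderate. These figures rest only on the plan's own formula and percentages, read in the order given.

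The consequence is conditional. If an intensity class is analysed or reported, the vigorous class is inverted and runs against the predicted direction. The literal moderate class and an analysis of mean heart rate do not reverse. The primary outcome (engagement) and the sample size are untouched. The sentence should be corrected before heart-rate data are scored, but it does not threaten the trial's main conclusion.

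**What to change.** Rewrite the one sentence in item 1.3 so that the bands do not overlap, using the plan's own two figures: moderate from 55% to below 70% of (220 minus age), and vigorous at 70% or above. The authors should reconcile the exact boundaries, including which band takes a value exactly on a cutoff, with reference 39, and make the scoring script agree.

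No time-in-band variable has to be added. Correcting the inequality is enough, and the analysed variable can stay as planned. The cost is one sentence, a check of the script, and notice of the change through the route in the Protocol amendments section.
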